## Abstract

**Background:**

Child mortality due to pneumonia is a major global health problem and is associated with hypoxemia. Access to safe and continuous oxygen therapy can reduce mortality; however, low-income countries may lack the necessary resources for oxygen delivery. We have previously demonstrated proof-of-concept that solar-powered oxygen (SPO_2_) delivery can reliably provide medical oxygen remote settings with minimal access to electricity. This study aims to demonstrate the efficacy of SPO_2_ in children hospitalized with acute hypoxemic respiratory illness across Uganda.

**Methods:**

*Objectives*: Demonstrate efficacy of SPO_2_ in children hospitalized with acute hypoxemic respiratory illness. *Study design:* Multi-center, stepped-wedge cluster-randomized trial. *Setting:* Twenty health facilities across Uganda, a low-income, high-burden country for pediatric pneumonia. *Site selection:* Facilities with pediatric inpatient services lacking consistent O_2_ supply on pediatric wards. *Participants:* Children aged < 5 years hospitalized with hypoxemia (saturation < 92%) warranting hospital admission based on clinical judgement. *Randomization methods:* Random installation order generated *a priori* with allocation concealment. *Study procedure:* Patients receive standard of care within pediatric wards with or without SPO_2_ system installed. *Outcome measures:* Primary: 48-h mortality. Secondary: safety, efficacy, SPO_2_ system functionality, operating costs, nursing knowledge, skills, and retention for oxygen administration. *Statistical analysis of primary outcome:* Linear mixed effects logistic regression model with 48-h mortality (dependent variable) as a function of SPO_2_ treatment (before versus after installation), while adjusting for confounding effects of calendar time (fixed effect) and site (random effect). *Sample size:* 2400 patients across 20 health facilities, predicted to provide 80% power to detect a 35% reduction in mortality after introduction of SPO_2_, based on a computer simulation of > 5000 trials.

**Discussion:**

Overall, our study aims to demonstrate mortality benefit of SPO_2_ relative to standard (unreliable) oxygen delivery. The innovative trial design (stepped-wedge, cluster-randomized) is supported by a computer simulation. Capacity building for nursing care and oxygen therapy is a non-scientific objective of the study. If successful, SPO_2_ could be scaled across a variety of resource-constrained remote or rural settings in sub-Saharan Africa and beyond.

**Trial registration:**

Clinicaltrials.gov, NCT03851783. Registered on 22 February 2019.

## Background

Globally, approximately 7.7 million children per year die before the age of five years. Infectious diseases account for a large proportion of these deaths, with pneumonia being the leading cause of mortality (2.1 million deaths/year) [1]. Most deaths occur in resource-constrained settings in Asia and Africa [2]. These countries report 2–10 times more children with pneumonia than industrialized countries [3]. In Uganda alone, child mortality is estimated to be 145,000 deaths per year [4]. Bacterial pneumonia, tuberculosis, sepsis, and severe malaria are common infectious etiologies, all of which lead to respiratory distress as a final common pathway. Oxygen (O_2_) therapy is essential to support life in these patients.

Large gaps remain in the clinical management of children presenting to African hospitals with respiratory distress, including essential supportive therapies such as supplemental O_2_. Despite being listed on the World Health Organization’s (WHO) list of essential medicines [5], O_2_ may not be available in hospitals and health centers in low- and middle-income countries (LMICs) because of cost and/or logistical challenges [6, 7]. Methods currently used in low-resource settings include compressed O_2_ cylinders and grid-powered O_2_ concentrators [8, 9]. Cylinders require supply chains linking O_2_ production plants to hospitals which may be compromised by poor road conditions, costs of transportation, and unstable supply chain management [8, 9]. O_2_ losses from cylinders can also vary greatly due to leakage [10, 11]. O_2_ concentrators, while shown to be more cost-effective and user-friendly than cylinders, depend upon a reliable and uninterrupted supply of electricity which is often unavailable in resource-constrained settings [8, 10]. A previous systematic review showed that 26% of health facilities in sub-Saharan Africa reported no access to electricity while only 28% of centers reported reliable access [12].

In resource-constrained settings, O_2_ delivery systems can lead to measurable improvements in survival from childhood pneumonia. A multi-hospital effectiveness study in Papua New Guinea demonstrated a reduction in mortality from childhood pneumonia from 5.0% to 3.2% (35% reduction in mortality) after implementation of an enhanced O_2_ delivery system [13]. We have previously described and implemented a novel strategy for O_2_ delivery that could be implemented in remote locations with minimal access to an electrical power supply: solar-powered oxygen (SPO_2_) delivery [14, 15].

SPO_2_ is an effective solution for supplemental O_2_ in low-resource settings [14–16]. Our systems have been described in detail previously and implemented at two hospitals in Uganda [14–16]. In brief, photovoltaic cells installed on the roofs of hospitals collect solar energy, which is stored as electricity in a battery bank, then used to power an O_2_ concentrator for production of medical grade O_2_. We previously demonstrated the feasibility, safety, and efficacy of SPO_2_ through a proof-of-concept study and a randomized controlled trial (RCT), showing clinical non-inferiority compared to cylinder O_2_ [14–16]. We enrolled 130 children with hypoxemia admitted to two Ugandan hospitals and showed that the length of stay was not prolonged in patients randomized to SPO_2_, relative to children randomized to cylinder O_2_ [15]. Further, we did not detect statistically significant differences in mortality between SPO_2_ and cylinder O_2_. Given its efficacy, before the widespread implementation of SPO_2_ across Africa and Asia, an evaluation of its impact on decreasing the mortality of children admitted with acute hypoxemic respiratory illness is required.

## Methods and design

### Objectives

This study aims to demonstrate the efficacy of SPO_2_ in children hospitalized with acute hypoxemic respiratory illness in Uganda. The study is a multicenter prospective evaluation of SPO_2_, using a stepped-wedge cluster-randomized design.

Our primary aim is to compare the 48-h mortality among children aged < 5 years admitted with hypoxemia before and after the implementation of SPO_2_ delivery at 20 hospitals in Uganda, adjusting for confounding effects of calendar time and site. As secondary aims, we will compare safety and efficacy outcomes among participants, monitor SPO_2_ system functionality and operational costs, and build capacity among nurses to deliver O_2_. The working hypothesis is that SPO_2_ can decrease the mortality of children admitted with hypoxemia Additional files 1 and 2.

### Study design

The study will be a stepped-wedge cluster RCT. This trial will not be blinded. Clusters (health facilities) will be randomly allocated to the timing of implementation of the SPO_2_ system. The installation of SPO_2_ will not be simultaneous but will proceed in accordance with the stepped-wedge design (Fig. 1). All health facilities will have a run-in period during which nurses will be trained in pulse oximetry, O_2_ management, and the study protocol. Data collection (prospective enrolment and accurate electronic record-keeping) will be in place by the end of the run-in period. SPO_2_ will be introduced one site at a time, on a monthly basis, until all 20 sites have SPO_2_ installed. The timing of installation of SPO_2_ will be random, with allocation concealment. Analysis will compare mortality before and after implementation of SPO_2_, using linear mixed effects (LME) logistic regression, adjusting for the confounding effects of time (fixed effect) and site (random effect) [17]. Data collection will continue until the trial’s termination, considered to be one month after the installation of SPO_2_ in the 20th site.

**Fig. 1 Fig1:**
[figure not shown]
Timeline for cluster-randomized stepped-wedge controlled clinical trial. The trial will involve 20 health facilities and 20 steps. Each step involves enrollment of patients at all sites for one month, with one new site installing SPO_2_ per month. Equipment installed at the health facilities will provide improved access to medical oxygen beyond the life of the study

### Setting

Uganda counts approximately 145,000 child deaths annually, of which 16% are attributed to pneumonia [4]. Uganda’s public healthcare system consists of health centers (levels II–IV), general/provincial hospitals, regional referral hospitals, and the National Referral Hospital. The majority of deaths occur in a limited number of general hospitals and level IV health centers where at least half have poor access to a stable electrical supply or O2 cylinders [18]. These represent ideal sites for early implementation of SPO_2_ because of a context-specific need for an O_2_ delivery system that does not rely on electrical power or cylinder distribution. We will enroll 20 sites in our cluster-randomized trial.

### Site selection

Health facilities were evaluated and selected based on the following criteria. Sites were included if they: (1) had pediatric inpatient services; (2) lacked consistent O_2_ supply on pediatric wards; and (3) had adequate space and willingness to install solar panels, a battery bank, and O_2_ concentrator on the hospital premises (i.e. on pediatric ward). Sites were excluded from the study if: (1) had no inpatient services for children; (2) had pre-existing, functional, and consistent O_2_ delivery systems (cylinder or concentrator); (3) did not have space or were unwilling to install solar panels, a battery bank, and O_2_ concentrator.

We conducted site visits to 44 health facilities across the country and interviewed key informants at each site. Based on site selection criteria, five sites were chosen from each of Uganda’s four geographic regions, for a total of 20 sites (Fig. 2). Additional “back-up” sites have also been identified, in case of difficulties with site re-engagement, site/personnel recruitment, or installation at one or more of the primary sites. Characteristics of the 20 chosen sites were as follows. While cylinder oxygen was available at 9/20 (45%) of sites, dedicated cylinders were not available on the pediatric wards of any health facility. Oxygen concentrators were present at 18/20 (90%) of sites, with only 4/18 (22%) of sites with dedicated concentrators available on pediatric wards. Concentrators were shared across wards in 11/18 (61%) sites. At the time of the interview, 11/18 (61%) concentrators were operational, and only 4/18 (22%) produced oxygen with ≥ 80% purity. Power outages were reported as frequent in 17/20 (85%) of sites. While 19/20 (95%) of sites had generators available, none turned them on when children needed oxygen. Because electricity is necessary to run oxygen concentrators, this suggested that access to a reliable power source is a major obstacle in delivering oxygen therapy. Overall, only 3/20 (15%) of sites had oxygen available for pediatric use.

**Fig. 2 Fig2:**
[figure not shown]
Sites for implementation and evaluation of solar powered O_2_ (SPO_2_) delivery. **a** Map of Africa showing Uganda (*black*). **b**
*Map* of Uganda showing SPO_2_ sites. Between four and six health facilities (District Hospitals or Level 4 Health Centers, HC IV) were chosen from each region (Central, Western, Eastern, and Northern) using the following criteria: facility has a pediatric inpatient ward; consistent O_2_ supply on pediatric ward is lacking; adequate space and willingness to install SPO_2_ system on pediatric ward. Sites are geographically distributed across the country and are likely representative of health facilities in sub-Saharan Africa where SPO_2_ would be cost-effective

Qualified site champions (local nursing leads) were recruited for each site to support SPO_2_ implementation.

### Participants

We will include patients presenting to the selected sites meeting the following inclusion criteria: (1) age < 5 years; (2) hypoxemia (SPO_2_ < 92%) based on non-invasive pulse oximetry taken within 24 h of admission, on room air; and (3) warrant hospital admission based on clinical judgement. Patients will be excluded from the study if: (1) measured SPO_2_ ≥ 92%; (2) they can be managed as an outpatient; (3) parents or guardians unwilling to provide written informed consent to participate in study; (4) known cyanotic cardiac condition; and (5) diagnosis of hypoxic ischemic encephalopathy in a neonate.

Screening procedures will be as follows: children aged < 5 years presenting to the participating facilities will be screened for hypoxemia using a portable pulse oximeter if they have cough and/or difficulty breathing. Past medical history will be reviewed with the parent or guardian for known cyanotic cardiac condition and/or hypoxic ischemic encephalopathy. If the patient meets eligibility criteria, the parent or guardian will be approached for informed consent.

### Randomization method

The random order of site installation will be generated before the trial. Site names will be written on paper and placed in sequentially numbered sealed opaque envelopes. Once a month, at the time of site selection for the next SPO_2_ installation, the next envelope will be opened to reveal the site. The envelope will be signed and dated, and all envelopes and records will be kept for quality monitoring purposes.

Randomization will be in blocks of four. Each block will include one site from each of four geographic regions of the country (Northern, Eastern, Western, and Central Regions). The order of the four regions within a block will be random; the selection of a site within the region will be randomly sampled without replacement. Thus, after each sequential block of four, the sites will be balanced by region.

### Study procedures

For eligible participants, the parent or legal guardian will be approached for consent to participate in the study (Additional file 3). If granted, the patient will be admitted to the pediatric ward, where there will be a SPO_2_ system installed or not, according to random timing of installation at each site. All patients will receive standard care for their underlying disease, including antibiotics for pneumonia, intravenous fluids as necessary, blood transfusion as necessary, antipyretics, and any other medical therapy required. The study will ensure there are no stock-outs of essential medications or equipment. Basic demographic and clinical data will be collected from the case admission record, and patients will be followed during their hospital admission. The primary outcome, death at 48 h after admission, will be recorded. Other outcomes could include death after 48 h, discharge, and transfer to another facility. Death at 48 h (versus other) will later be analyzed as a binary variable. Patients discharged or transferred to another facility will be followed up by telephone at 48 h after admission to assess status.

During hospitalization, secondary outcomes will be recorded, including vital signs at admission and daily thereafter until discharge. Oxygen saturations will be monitored on a 4-hourly basis, during oxygen administration and after. Oxygen utilization (flow rate, duration) will be recorded throughout hospitalization. The need for oxygen therapy will be assessed daily, using standardized criteria for weaning oxygen. The length of stay among survivors will be recorded, as well as the final patient disposition (discharged without disability, discharged with disability, transferred to another facility, or death). The participant flow is illustrated in Fig. 3.

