### Outcome measures

Our study’s primary endpoint is mortality at 48 h after admission. We will also evaluate several secondary outcome measures, including in-hospital mortality (time to death), length of hospital stay, duration of supplemental O_2_ therapy (time to wean O_2_), O_2_ delivery system failure(s), cost (installation, servicing, and maintenance), baseline and retained nursing skills in managing oxygen therapy, etiology (based on polymerase chain reaction of dried blood sample and nasopharyngeal swabs), as well as diagnostic and prognostic host biomarkers (Additional file 4).

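### Oxygen duration partly measures supply in control time, and length of stay among survivors compares groups that the intervention is expected to change

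*Protocol article*

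**What the plan says.** Outcome measures lists, among the secondary outcomes, "length of hospital stay, duration of supplemental O_2_ therapy (time to wean O_2". Stay carries no survival restriction there, and time to wean appears as a gloss on oxygen duration. Study procedures is narrower on stay: "The length of stay among survivors will be recorded". The same section records oxygen flow and duration as utilisation, and adds: "The need for oxygen therapy will be assessed daily, using standardized criteria for weaning oxygen".

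Site selection shows what control time looks like. Facilities were eligible if they "lacked consistent O_2_ supply on pediatric wards", and at the site visits "only 3/20 (15%) of sites had oxygen available for pediatric use".

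Statistical considerations plans comparative analyses of the secondary outcomes, with mixed models where possible, between SPO2-treated and untreated patients.

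**The concern.** Each outcome can move for a reason other than recovery.

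- **Oxygen duration.** After installation, therapy should end mainly when the child no longer needs it. Before installation it may never start, or may stop because supply stops. A difference between conditions then partly measures access to oxygen, which is the intervention itself. Read as time to wean, a longer duration under SPO2 would look like slower recovery.
- **Stay among survivors.** Survival is what the trial expects to change. If SPO2 saves very ill children, they enter the survivor group only in the SPO2 period. If they also stay longer than the others, mean stay rises although no child is worse off.

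At stake is the interpretation of two patient-level secondary results that will be read beside the mortality result.

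**Working it through.** The article gives no figure for stay or oxygen duration, so there is none to reproduce. The checks use its mortality inputs and, where it is silent, assumptions marked as such.

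**Inputs from the article**
- Baseline mortality 15% and relative reduction 35% (Fig. 4 caption), so mortality after installation is 0.15 × 0.65 = 9.75%.
- Oxygen for pediatric use at 3 of 20 sites, 15%, at the site visits (Site selection).

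**1. Share of SPO2-period survivors who would have died under control**
- Survivors: 85% under control, 90.25% under SPO2.
- f = (0.9025 − 0.85) / 0.9025 = 0.0525 / 0.9025 = 5.8%.
- Per 1200 admissions in each condition: 1020 versus 1083 survivors, so 63 additional children.

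**2. Shift in mean stay among survivors**
- Shift = f × e − b. Here e is the extra days that rescued children stay relative to other survivors in the same condition, and b is any true shortening of stay. Both are assumed.
- With b = 0: e = 2, 4 or 6 days gives +0.12, +0.23 or +0.35 day.
- With b = 0.25 day: e = 5 gives 0.29 − 0.25 = +0.04 day, so the gain is hidden. With e = 2 it is 0.12 − 0.25 = −0.13 day, so the gain still shows.
- The sign reverses only when b is below about 0.058 × e.

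**3. Stay without the survivor restriction**
- Assume 5 days for survivors and 1 day for deaths.
- Control: 0.85 × 5 + 0.15 × 1 = 4.40 days.
- SPO2: 0.9025 × 5 + 0.0975 × 1 = 4.61 days.
- The shift is +0.21 day with no change in any survivor's stay, similar in size to the bias in step 2.

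**4. Oxygen duration**
- Mean days = availability × days needed × (1 − true shortening).
- Assume a need of 3 days and 95% availability after installation.
- Control at 15%, 50% or 75% availability: 0.45, 1.50 or 2.25 days.
- SPO2 with no true shortening: 0.95 × 3 = 2.85 days. With a true 20% shortening: 2.85 × 0.8 = 2.28 days.
- Even with the 20% shortening, SPO2 shows the longer duration at all three control levels, though at 75% the two are almost equal. The crossover is at control availability 0.95 × 0.8 = 76%, whatever the days needed.
- Death adds a smaller shift in the same direction. With full supply in both conditions and deaths at day 1, control is 0.85 × 3 + 0.15 × 1 = 2.70 days and SPO2 is 0.9025 × 3 + 0.0975 × 1 = 2.81 days.

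**The case against.** The strongest reply is that the article fixes less than this implies. Study procedures says what is recorded, Outcome measures lists stay without restriction, and the detailed analysis may sit in an analysis plan that is not shown. Final disposition and time to death are also collected, so a competing-event analysis remains open. That is fair, and it is why the fix is cheap. It does not remove the point: the article itself writes two versions of stay, equates duration with time to wean, and announces treated-versus-untreated comparisons. Neither version of stay is free of the problem (steps 2 and 3).

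It can also be said that oxygen duration is already recorded under utilisation and that no sentence calls a shorter duration a benefit. This stands in part. The outcomes are labelled secondary, and efficacy is named only as a category in the secondary aims. The time-to-wean gloss nevertheless invites a recovery reading.

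The pledge in Study procedures to prevent stock-outs of essential medicines and equipment might be taken to cover oxygen in control time. That would remove the contrast with unreliable supply on which the trial rests.

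Three stronger inferences are not supported:
- A reader might infer that control duration is zero at 17 of 20 sites. The 3 of 20 figure is a pre-trial snapshot. Concentrators were present at 18 of 20 sites and cylinders at 9 of 20, staff are trained in oxygen management during run-in, and availability during control time is not given.
- A reader might infer that length of stay is necessarily biased against SPO2. The hypothesis concerns mortality only, and the direction depends on how long rescued children stay, for which the article has no data.
- A reader might take the Discussion's remark that stay can be assessed unambiguously as a claim of unbiased comparison. In context it contrasts stay with microbiological etiology, which cannot be established at these sites.

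**Conclusion.** The point holds for both outcomes, with unequal force. For oxygen duration the mechanism is documented and the distortion can be large: under the assumptions in step 4, SPO2 shows the longer duration whenever control availability is below 76%, even with a true 20% shortening of need. The need, the post-installation availability and the control availability are all assumed.

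For stay among survivors the possible bias is modest, about 0.06 day per extra day that rescued children stay. The 5.8% behind it uses 48-h mortality as a stand-in for in-hospital death and assumes that SPO2 causes no deaths. The sign reverses only if rescued children stay much longer than the others or the true gain is small.

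The mortality comparison does not depend on either outcome.

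**What to change.** 1. Reconcile Study procedures and Outcome measures on length of stay. Analyse time to live discharge in all enrolled children, with death as a competing event or ranked worst. Stay, disposition and time to death are already collected, so this costs only wording.
2. Report oxygen duration as a descriptive utilisation measure, not as evidence of efficacy or recovery, and drop its equation with time to wean. This also costs only wording.
3. Add time until oxygen is first judged no longer needed, with death competing, only if the daily assessment is recorded for every enrolled child whether or not oxygen was given. It should not be assumed that these data exist: the article says "The need for oxygen therapy will be assessed daily" but ties this to weaning criteria, and describes saturation monitoring as taking place while oxygen is given and afterwards. The cost is possible extra recording for control-period children in a trial that is already recruiting.

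None of these changes alters a treatment rule.
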